## Abstract

**Background:**

The present randomized controlled trial, which is crossed with the “PREVenting the impairment of primary Osteoarthritis by high impact long-term Physical exercise regimen” Main Medical Trial (PrevOP-MMT), aims to evaluate a psychological adherence program (PrevOP-PAP), and is designed to support persons with knee osteoarthritis (OAK) in the uptake and maintenance of regular physical activity to reduce OAK symptoms. The PrevOP-PAP is based on the Health Action Process Approach (HAPA), a social-cognitive theory predicting health behavior change in individuals, extended here by social network characteristics and social exchange processes. It is expected that participants with OAK receiving the PrevOP-PAP will maintain higher levels of regular physical activity throughout a 24-month period and consequently report lower levels of OAK symptoms than participants of an active control condition.

**Methods:**

A total of *N* = 240 participants with medically verified moderate OAK will be randomly assigned to an intervention condition (PrevOP-PAP-I; 50%) or an active control condition (PrevOP-PAP-CTRL). The PrevOP-PAP-I includes a motivational intervention, repeated self-regulation interventions, and a network creation intervention delivered over 12 months. Modes of intervention delivery include a paper-pencil motivation leaflet with a quiz, a computer-assisted face-to-face intervention, four computer assisted phone-based interventions, and activity calendars. The PrevOP-PAP-CTRL includes the motivational intervention only. Primary outcome will be OAK symptoms. Secondary outcomes include objectively and subjectively measured physical activity and indicators of quality of life. Other outcomes are HAPA-derived self-regulatory indicators as well as proposed social network and social exchange mechanisms of health behavior change. Assessments take place at baseline, 6 months, 12 months, 18 months, and 24 months following baseline.

**Discussion:**

Based on the extended HAPA, this study seeks to reveal the self-regulatory and social mechanisms of the uptake and maintenance of physical activity and their relation to disease symptoms in persons with OAK. The design and evaluation of this program are intended to become a yardstick for future development and implementation of digitalized psychological adherence programs in this population.

**Trial registration:**

German Clinical Trials Register; also available at http://apps.who.int/trialsearch/; registration number: DRKS00009677; date of registration: 26 January 2016.

## Background

The main objectives for physical activity (PA) prescribed to persons with osteoarthritis of the knee (OAK) are enhancing the mobility and required range of motion of the joint, increasing the force and endurance of the muscles, and reducing pain [1, 2]. Guidelines advise persons with OAK to engage in joint-friendly regular moderate to vigorous PA (aerobic; moderate: at least 150 min per week, or vigorous: at least 75 min per week, or a mixture of both, on at least five days a week, best performed in bouts of at least 10 min) and regular muscle-force strengthening exercises [3]. Such regular PA requires self-regulated action and, therefore, becomes subject to adherence failure [4, 5]. There is no medical solution to this problem, but a psychological adherence program teaching self-regulation strategies to support uptake and maintenance of regular PA may make a substantial contribution [4, 6–8].

Health psychology research has identified various self-regulation strategies to facilitate motivation, to prevent relapse, and to support PA maintenance, based on theory and empirical evidence [9–15]. The present project uses the Health Action Process Approach (HAPA; Fig. 1) as a theoretical backdrop that includes factors predicting intention formation (i.e., motivational stage) and specifies a mediating sequence of factors leading up to the implementation and maintenance of action (volitional stage), in this case, regular PA [16]. The HAPA is a hybrid model of behavior change that is derived from several preceding social cognitive models [17–21]. In the motivational stage, three factors are proposed to strengthen intention formation to change health-relevant behaviors: task self-efficacy or the belief that one is capable of performing the behavior in question, outcome expectancies or a decisional balance of pros and cons associated with behavior change, and risk perception regarding health consequences if behavior is not changed. Several other self-regulatory factors are then proposed to mediate between intention and behavior in a volitional stage, including planning, maintenance self-efficacy, recovery self-efficacy, and action control [16]. Planning contains strategies that help the individual to implement behavior by a-priori linking situational cues with the intended behavior change (action planning) and strategies that additionally facilitate risk management by anticipating barriers and linking them with planned behavioral alternatives (coping planning). Maintenance self-efficacy and recovery self-efficacy refer to the subjective belief that one is capable to maintain behavior change for an extended amount of time or resume it once a lapse has occurred, respectively. Action control is composed of three subfacets including awareness of standards or intentions, self-monitoring of the actual behavioral response, and regulatory efforts should the current behavior diverge from what was intended [16, 22]. Additional resources of behavior change, such as use of social exchange strategies (e.g., social support, see below) are also suggested to impact intention formation and behavior (Fig. 1).

**Fig. 1 Fig1:**
[figure not shown]
The Health Action Process Approach (HAPA; [16])

Respective theory-based intervention strategies to facilitate adoption and maintenance of PA include intention formation by goal setting, inducing positive outcome expectancies, and task self-efficacy as well as volitional strategies that guide participants in their formulation of action plans, coping plans, and practice of continuous action control [10, 14, 23]. Evidence from HAPA intervention studies yields results for populations with various chronic illnesses and disabilities [14]. Especially planning interventions and action control programs proved to be successful. Evidence has emerged in the context of orthopedic and cardiac rehabilitation [10, 22, 24]. Randomized controlled trials have documented the evidence in favor of planning interventions [25, 26]. When addressing action planning and coping planning separately in interventions, different effects were found: Persons in cardiac rehabilitation became more active when both kinds of planning were addressed in the intervention, as opposed to a mere action planning intervention [27]. In orthopedic interventions, coping planning seemed to be of particularly high importance for long-term maintenance [10]. Self-monitoring as part of action control is an essential behavior change technique that can be applied to various health behaviors. When people keep records of their behaviors in form of a diary, checkmarks in their calendar, or by using electronic messaging, they become aware of gains and deficits in the implementation of behavior change which allows them to take further regulatory action [22, 23]. In addition to intensive action control regimens, a specific strategy to prevent relapse into sedentary behavior includes booster sessions [10, 24]. Follow-up intervention boosters refer to brief contacts beyond the main part of the intervention to reinforce previous intervention content [10]. Adding booster sessions to an initial face-to-face intervention and thus supporting the maintenance of self-regulation strategies can be one way to achieve behavior maintenance. In the clinical context, telephone-delivered intervention boosters have been successfully implemented to promote exercise maintenance [10, 24].

As persons’ close social network members (e.g., spouses, family, sports companions) often try to and succeed in co-regulating an actor’s health behavior, an extension of core predictors of individual health behavior change to include network formation and emergent social exchange strategies with important others is called for [28–30]. Recent findings suggest that by including another person into the behavior change process, e.g. by dyadically planning an individual actor’s health behavior change together with a planning partner, a number of potentially beneficial processes are triggered [12, 31, 32]. These include enhanced self-regulatory action control by the actor, but also a number of social exchange processes initiated by the planning partner that may help the actor maintain behavior change, including social support and social control [31, 32]. Social support refers to assistance from others that may help a recipient achieve specific behavioral goals [33, 34]. Social control, on the other hand, refers to strategies that aim at influencing or regulating another person’s behavior, such as direct persuasion, pressure, nagging or positive reinforcement of desired behavior [35]. Whereas social control may be a double-edged sword with the capacity of supporting, but also compromising the behavior change process [36, 37], it is likely to be triggered in interventions addressing network formation and therefore needs to be accounted for. In accord with Bodenmann’s cascade model [38], social exchange strategies may be especially effective in the long run, when initial self-regulation starts to wear out [39]. Moreover, social exchange strategies were shown to be prospectively associated with several self-regulatory processes reviewed above and may thus serve as a real-life booster of them [30, 36].

Although a vast amount of research on physical activity in persons with OAK has already been performed, most of it is not theory guided [1, 2, 40], and therefore, innovative theory-based programs for exercise maintenance are needed. In particular, the roles of action control, network formation, and social exchange strategies that support and maintain self-regulatory processes over a longer period of time need further investigation. Therefore, the present research design includes multiple treatment occasions and measurement points over an extended period of two years.

### Aims and primary research question

The present randomized controlled trial (RCT) is crossed with the “PREVenting the impairment of primary Osteoarthritis by high impact long-term Physical exercise regimen (PrevOP)”-Main Medical Trial (henceforth referred to as PrevOP-MMT; see [name] et al. Preventing the impairment of primary osteoarthritis by high impact long-term physical exercise regimen (PrevOP): Study protocol of a randomized controlled trial. Manuscript in preparation.). Using the HAPA [16] as a theoretical backdrop and extending it with network characteristics and emergent social exchange processes that are proposed to facilitate behavior change, this project develops and evaluates a theory-based PrevOP-Psychological Adherence Program (henceforth referred to as PrevOP-PAP). The PrevOP-PAP is designed to strengthen long-term self-regulation in the adoption and maintenance of PA by using regular boosters of main intervention contents and by facilitating social network creation that is proposed to result in the additional social exchange processes supporting the maintenance of regular PA. The initiation and maintenance of regular PA is in turn proposed to be a behavioral predictor of reduced OAK symptoms (as assessed by the Western Ontario and Mc Master Universities Osteoarthritis Index [WOMAC]). Because the PrevOP-PAP intervention addresses predominantly volitional factors, the efficacy of the intervention condition will be compared to an active control condition; both conditions involve a brief motivational treatment [16].

#### Primary research question

Compared to an active control condition, can a theory-based psychological adherence program designed to increase self-regulation and network formation facilitate the uptake and maintenance of regular PA (key secondary outcome) and contribute to a reduction in symptom severity (primary outcome) in persons with moderate OAK?

## Methods

### Design

The PrevOP-PAP trial shares participants, inclusion-, and exclusion criteria with the PrevOP-MMT (crossed design). In the PrevOP-MMT, participants with OAK (*N* = 240), a randomized 33% of whom receiving a high impact long-term physical exercise regimen (PrevOP-MMT-HIE) with resistive vibration exercise, 33% receiving a low-impact long-term exercise regimen (PrevOP-MMT-LIE) and 33% receiving no structured or monitored exercise regimen (PrevOP-MMT-CTRL;), are again randomly subdivided into 50% who undergo the PrevOP-PAP intervention (PrevOP-PAP-I, *n* = 120) and another 50% who serve as active controls (PrevOP-PAP-CTRL, *n* = 120). Forty participants are thus randomly assigned to each of 6 (3 PrevOP-MMT * 2 PrevOP-PAP conditions) study conditions and then collapsed into either the PrevOP-PAP-I (*n* = 120) or the PrevOP-PAP-CTRL (*n* = 120) (see Fig. 2).

**Fig. 2 Fig2:**
[figure not shown]
Conditions of the PrevOP-Main Medical Trial (PrevOP-MMT;) nested in the PrevOP-Psychological Adherence Program (PrevOP-PAP) conditions (PrevOP-PAP-I and PrevOP-PAP-CTRL)

Data are assessed at baseline (T0), 6 months (T2), 12 months (T3), 18 months (T4), and 24 months (T5) via self-report measures and three one-week assessment periods (T0, T3, T5) when participants wear accelerometers for one-week periods each. Within the PrevOP-PAP-I, the main computer-assisted face-to-face intervention takes place at T1 (one week following T0), additional action control and booster intervention phases take place between week 1 and week 4, between week 25 and week 28, and between week 50 and week 53 following baseline (T0), using computer-assisted phone-based interventions and paper-pencil activity calendars (i.e., action control intervention, see below). Initial self-report assessments and the computer-assisted face-to-face intervention are done at the study center at Charité – Universitätsmedizin Berlin. Accelerometers are worn for one-week periods in daily life during wake time. For computer-assisted phone-based interventions, participants are called at home. Activity calendars are completed daily at participants’ homes for three periods of four weeks each (see Fig. 3). Participants receive a lump-sum travel cost reimbursement of EUR 5 per study center visit (assessment or intervention sessions). The ethics committee of the Charité – Universitätsmedizin Berlin approved this study (EA4/027/15).

**Fig. 3 Fig3:**
[figure not shown]
SPIRIT chart of the PrevOP-PAP trial. W: Week. M: Month. T: Time. PrevOP-PAP-I: PrevOP Psychological Adherence Program Intervention condition. PrevOP-PAP-CTRL: Psychological Adherence Program ConTRoL condition

### Sample and recruitment

A total of 240 persons with OAK aged between 40 and 80 years will be recruited for participation in all parts of the study (i.e., PrevOP-MMT and PrevOP-PAP) by the PrevOP-MMT study staff. Reactive recruitment strategies will include flyers, social media, press-releases, and interviews asking those interested to contact the study center. Proactive recruitment strategies will include mailings in stratified age and gender groups as determined by local registration offices and recruitment of patients from the project-associated ambulatory clinic. Inclusion and exclusion criteria are relevant mostly for the PrevOP-MMT. They are as follows:

#### Inclusion criteria

Ambulatory men and women aged between 40 and 80 years with OAK grades 2 and 3 following the Kellgren and Lawrence classification [41], according to American College of Rheumatology criteria [42] with pain on at least half of the days of the previous month (intensity > 40 mm on a 100 mm visual analogue scale). Radiographical signs will include Kellgren and Lawrence grade 2 (i.e., definite osteophytes and possible narrowing of joint space) or grade 3 (i.e., moderate multiple osteophytes, definite narrowing of joint space and some sclerosis, and possible deformity of bone ends), and joint space width of 2.5 to 5 mm with predominant knee osteoarthritis of the medial tibiofemoral compartment, written informed consent.

#### Exclusion criteria

Knee total endoprothesis at any time, hip total endoprothesis during the last 12 months, participation in other clinical trials, cognitive impairment, insufficient comprehension of the German language. During the past 5 years: cancer, angina pectoris, coronary intervention, thromboembolic events (acute deep venous thrombosis, pulmonary embolism, stroke, myocardial infarction, arrhythmia absoluta, uncontrolled hypertension, retinal artery occlusion, vena centralise retinae occlusion). Paraplegia, hemiplegia, severe rheumatoid arthritis, severe polyneuropathy, severe vertebral disc prolapse, severe spinal canal stenosis, dementia, acute tendinitis (legs only), current fractures (pelvic and legs), cholecystolithiasis, kidney stones, urethral stones, hernia abdominalis and/or inguinalis, acute migraine, current wounds (pelvis and legs), epilepsy, pregnancy. Recent intra-articular injection (notably glucocorticoids < 3 months previously or hyaluronic acid < 6 months previously), clinical deformities, and previous treatments acting on cartilage, oral glucosamine ≥1500 mg/day and chondroitin sulphate < 3 months previously).

Inclusion and exclusion criteria are checked by the PrevOP-MMT’s medical personnel during a first screening telephone interview and a subsequent appointment for extensive medical screening assessments at the study center. Informed consent and inclusion into the study takes place at the beginning of baseline assessments (T0) and is done by the PrevOP-MMT’s medical personnel, when participants receive extensive information on the study procedure (PrevOP-MMT and PrevOP-PAP parts; oral and written) including randomization procedures, provide written informed consent, and then begin their first period of assessments.

### Power analysis

For the PrevOP-MMT a sample size of *N* = 240 has been determined. For the PrevOP-PAP, choosing an alpha level of .05 and a stability factor of .68 of the WOMAC (www.rheumatology.org), a minimum sample size of *n* = 122 is required which includes 2 groups at 5 points in time up to the primary endpoint (baseline to 24 months) to detect a small effect (*f* = 0.1) of a within by between subjects factors interaction with a power of .95. With an expected drop-out rate of 20%, the required sample size increases to *n* = 153. This required sample size for the PrevOP-PAP trial is thus in accord with the PrevOP-MMT-required inclusion of *N* = 240 participants.

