#### Hypotheses tests

Longitudinal mediation analyses will be conducted using manifest path analyses. PrevOP-PAP-condition will be specified as a dummy-coded independent variable, accelerometer-assessed MVPA as a mediator (in minutes per week), and WOMAC scores as the primary outcome (controlling for respective baseline assessment). Dummy-coded PrevOP-MMT-conditions will be routinely tested as moderators of the association between MVPA (mediator) and WOMAC (primary outcome). If no interactions occur, PrevOP-MMT-conditions are tested as simple-effect covariates and dropped only if they are not related to the mediator or primary outcome. Further covariates are determined by results of the randomization check and bivariate correlations of assumed covariates with primary or secondary outcomes. Significance of all indirect effects will be tested using bootstrapping methods.

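### The power calculation is for a group-by-time interaction on WOMAC, but the hypotheses are tested by an indirect effect with no stated power, and the effect called small is about half an SD

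*Protocol article*

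**What the plan says.** The Power analysis section of the protocol article sets its inputs by "choosing an alpha level of .05 and a stability factor of .68 of the WOMAC", with 2 groups, 5 time points from baseline to 24 months, and f = 0.1. It concludes that "a minimum sample size of *n* = 122 is required" and describes the aim as "to detect a small effect" "of a within by between subjects factors interaction with a power of .95". An expected drop-out of 20% raises the number to 153. The section notes that this fits within the 240 participants already required by the main medical trial.

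The Hypotheses tests section plans something else: a manifest path model from adherence-program condition, through accelerometer-assessed moderate-to-vigorous activity (MVPA), to WOMAC, with baseline controlled. Its only statement about significance testing is "Significance of all indirect effects will be tested using bootstrapping methods".

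A mixed model of within-person change in the primary outcome by study condition appears under Additional analyses. The mixed models described earlier in the statistical section serve as manipulation checks. According to the Design section, accelerometers are worn at T0, T3 and T5 only.

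**The concern.** Two things do not fit together.

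1. The stated power belongs to an analysis that the article lists as additional. The analysis under the hypotheses heading is a product of two paths, program to MVPA and MVPA to WOMAC. Its power depends on the size of both paths and on a mediator measured at three waves, not five. None of this enters the calculation.

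2. The label small is attached to an f whose meaning depends on the repeated-measures setup. In a plain two-group comparison f is half the standardised difference, so f = 0.1 would be 0.2 SD. In a 2 × 5 interaction it is considerably more.

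At stake is how a null result is read. Someone told that the trial has 95% power for a small effect could take a non-significant indirect effect, or a non-significant WOMAC difference, as ruling out a small benefit. The calculation supports neither conclusion.

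**Working it through.** **Inputs from the Power analysis section:** alpha .05, correlation r = .68, k = 2 groups, m = 5 times, f = 0.1, power .95, drop-out 20%. Enrolment is 240, so 240 × 0.8 = 192 completers.

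**Step 1. Reproduce the stated figure.** Repeated-measures ANOVA, within-between interaction, sphericity assumed:

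- λ = f² × N × m / (1 − r) = 0.01 × 122 × 5 / 0.32 = 19.06
- df = (k − 1)(m − 1) = 4 and (N − k)(m − 1) = 120 × 4 = 480
- Power = .953 at N = 122 and .9499 at N = 120, so 122 is the smallest even N that reaches .95.
- 122 / 0.8 = 152.5, rounded up to 153.
- Power for the same test at 192 completers is .997. If sphericity fails with epsilon = 0.75 (assumed), power is .90 at 122 and .986 at 192.

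The plan's arithmetic is right.

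**Step 2. Convert f = 0.1 into an arm difference.** With equal baselines and arm difference d(t) in SD units, the interaction cell effects are ±[d(t) − mean d]/2. So f is half the standard deviation of d(t) over the five times. Per unit of the largest difference:

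| Pattern T0, T2, T3, T4, T5 | SD of pattern | f per 1 SD | Difference at f = 0.1 |
|---|---|---|---|
| 0, 1, 1, 1, 1 (constant from 6 months) | .400 | .200 | 0.50 SD |
| 0, ¼, ½, ¾, 1 (linear) | .354 | .177 | 0.57 SD |
| 0, 0, 1, 1, 1 (constant from 12 months) | .490 | .245 | 0.41 SD |

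**Step 3. Power of the interaction test if the true difference were 0.2 SD.** This value is an assumption; the article gives none in SD units. Then f = 0.2 × the third column:

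| Pattern | f | Power, N = 122 | Power, N = 192 |
|---|---|---|---|
| Linear | .035 | .197 | .299 |
| Constant from 6 months | .040 | .246 | .379 |
| Constant from 12 months | .049 | .361 | .550 |

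**Step 4. A direct comparison for scale.** Baseline-adjusted 24-month contrast with r = .68 and 192 completers:

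- SE = √[4 × (1 − .68²) / 192] = √[4 × .5376 / 192] = .106 SD
- 80% power: (1.96 + 0.84) × .106 = 0.30 SD
- 95% power: (1.96 + 1.645) × .106 = 0.38 SD
- At 0.5 SD the power is .965 with N = 122 and .997 with N = 192. At 0.2 SD it is .47 with N = 192.

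**Step 5. The planned indirect effect.** The article gives no path sizes, so only a range can be shown. Approximate the power as power(a path) × power(b path). Here a is the program effect on MVPA in SD, adjusted for a baseline correlation assumed to be .68, and b is the standardised MVPA–WOMAC path. At N = 192:

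- a = 0.2, b = .10: .472 × .285 = .135
- a = 0.5, b = .14: about .50
- a = 0.5, b = .20: about .81
- a = 0.5, b = .40: above .99

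The answer depends almost entirely on values that the article does not state.

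**The case against.** The strongest reply is that nothing in the Power analysis section is miscalculated. It names its test, prints its f, and the figure reproduces. A reader might infer from the mismatch that the trial does not have the power it states. The documents do not support that: for the stated interaction, enrolment of 240 exceeds the 153 required, and 192 completers give about .997. A half-SD difference would also be well covered by a direct 24-month comparison.

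A reader might also infer that the mediation test is underpowered. That is not shown either. The Hypotheses tests section controls for baseline, and with baseline adjustment the power runs from low to near certain depending on the assumed paths. It is unsupported rather than demonstrably below .95.

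It is also fair to say that the powered analysis is not absent from the plan. The mixed model under Additional analyses is essentially that test, so the defect lies in how the analyses are ranked. Finally, calling f = 0.1 small follows a common convention on the f scale, the value is printed, and the article never claims power for 0.2 SD.

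All of this stands. What remains is that the only stated power attaches to an analysis labelled additional, that the hypothesis test has none, and that the label small, without a WOMAC difference beside it, suggests a sensitivity the calculation does not provide.

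**Conclusion.** The point holds as a mismatch between the sample-size justification and the planned hypothesis test, together with a misleading effect label. It is not an arithmetic error and not a shortage of participants.

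The detectable difference behind the stated .95 at 122 participants is 0.41 to 0.57 SD of WOMAC. This assumes equal baselines, sphericity and one of the time patterns shown. For a true difference of 0.2 SD, which is an illustrative assumption, the interaction test has about 20–36% power at 122 and 30–55% at 192. The power of the indirect-effect test cannot be derived from the article.

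**What to change.** Choose one of two routes in the text.

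1. Name the condition-by-time model of WOMAC, now under Additional analyses, as the primary efficacy test, and make the mediation analysis secondary or explanatory. The stated power then applies, provided that time enters as five categories, as in the calculation.
2. Keep the indirect effect as the hypothesis test and state its power, with the assumed program-to-MVPA and MVPA-to-WOMAC paths and the baseline correlations of both variables.

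On either route, replace the label small with the implied WOMAC difference (0.41–0.57 SD at n = 122). If the sponsor prefers to name a baseline-adjusted 24-month contrast, the statement would be about 80% power for 0.30 SD and 95% for 0.38 SD, with 192 completers and r = .68.

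The cost is wording only, and N = 240 does not change. The downside is that the published power statement becomes less favourable.
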